#### Hopelessness

Hopelessness is to be measured with Beck's Hopelessness Scale [43] (BHS), a 20-item measure pertaining to the global experience of hopelessness, modified from a simple True/False format to a 5-point Likert-style rating system. It has a strong internal consistency (.81 to .90 in different studies).

#### Quality of Life

We administer the OQ-45 [44] (Outcome Questionnaire 45) to assess well-being. Quality of Life is an important measure in RCTs because an increase in patient's subjective well being motivates them to generalize what they learn during the treatment [45].

### Explanatory variables

#### Coping

The Coping Inventory for Stressful Situations [46] (CISS) is a 48-item self-report measure of coping. The measure is divided into three subscales, each containing 16 items: task-oriented coping, emotion-oriented coping, and avoidance-oriented coping. Respondents are asked to rate on a 5-point scale how each item is representative of their own way of coping with stress. The CISS has adequate psychometric properties. Across studies, the CISS has proved to be reliable. The internal consistency of the sub-scales is excellent (alpha > 0.85) [47].

#### Time Fluency

Our adapted version of MacLeod's Future Thinking Task [48] (FTT) is used to determine both positive and negative ideas about the past, present and the future. MacLeod's fluency task consists of three future time periods: the next week, the next year and the next five to ten years. Subjects are given 30 seconds to verbally provide examples for each time period: things they are looking forward to, and things they are not looking forward to. Our adapted version also inquires about current and past time periods, and assesses the emotional relevance of the experiences and their subjective significance for the future.

#### Time Perspective

Zimbardo's Time Perspective Inventory [49] (ZTPI) provides information about the time perspectives of the participants. The ZTPI consists of 56 items that are assessed on a 5-point Likert Scale, ranging from (1) very untrue to (5) very true. It has a high test-retest reliability ranging from .70 to .80 for the different factors.

#### Transcendental Future thinking

Another time related instrument is the additional scale of the ZTPI called the Transcendental Time Perspective Inventory (TFTPI), measuring what Boyd & Zimbardo [50] called transcendental future thinking: one's ideas about the afterlife as a motivating factor in one's present behaviour. The TFTPI consists of 10 statements. Participants rate these statement on a 5-point Likert scale (see ZTPI).

#### Social Problem Solving

The Social Problem-Solving Inventory-Revised [51] (SPSI-R) consists of 52 items that respondents rate on a 5-point scale. The SPSI-R has five scales: Positive Problem Orientation (PPO, 5 items), Negative Problem Orientation (NPO, 10 items), Rational Problem Solving (RPS, 20 items), Impulsivity/Carelessness Style (ICS, 10 items), and Avoidance Style (AS, 10 items). Alpha values for these five scales range from .76 to .92 and test-retest reliability ranges from .72 to .88.

#### Analyses

We are particularly interested in the effect (Cohen's *d*) on the main parameter suicide ideation. The effectiveness analyses will be conducted according to both intention-to-treat (ITT) and treatment completers principles. In the ITT analysis all randomized participants in the treatment group are included, irrespective of adherence, actual treatment received, or withdrawal from treatment or assessment. The completers analysis will focus on those participants who took part in 80% or more of the sessions and completed the post measurement.

Descriptive and mediating variables will be analyzed in order to reveal variables that need to be taken into account as covariates in the primary analyses of treatment effects. In order to find differences between the effects of our Future Oriented Group Training and treatment as usual we will perform analyses of repeated measures. We expect data loss due to drop out of participants. By using latent random effects variables for each participant multi level multivariable analysis permits estimation of changes in repeated measures, even when not all post assessment data are available due to missing data.

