### Sample Size

The effect size deemed worthwhile to be detected by the study is *d *= 0.5. This is what is generally judged to be a clinically relevant effect size [39]. Power calculations are based upon a type I error α = 0.05, a power of 0.80, and an effect size of 0.5, imply a minimum of 63 participants in the groups. We calculated power to be sufficient for both intention-to-treat and completers analysis. Expecting that 80% of the patients in the 'suicide ideations group' are willing to participate (before randomization), and a drop out of 20% after randomization, we need to include 75 patients in each of the two groups to maintain 63 completers.

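### The completers set is selected by different rules in the two arms after randomisation, yet it stands unranked beside ITT as an effectiveness analysis and is included in the power claim

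*Protocol article*

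**What the plan says.** All references are to the protocol article.

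- **Standing of the analyses (Analyses):** "The effectiveness analyses will be conducted according to both intention-to-treat (ITT) and treatment completers principles". Neither is named as the deciding one.
- **ITT set (Analyses):** "In the ITT analysis all randomized participants in the treatment group are included", whatever their adherence or withdrawal. The sentence does not mention the control group.
- **Completers set (Analyses):** "The completers analysis will focus on those participants who took part in 80% or more of the sessions and completed the post measurement".
- **Sessions (Experimental Condition, Control Condition):** the training consists of 10 weekly group sessions, given only in TAU+. Controls receive treatment as usual, and no session count is described for them.
- **Power (Sample Size):** power is said to be sufficient for both the ITT and the completers analysis. The section plans 75 patients in each group so that 63 completers remain.
- **Model (Analyses):** a repeated-measures multilevel model with random effects per participant, so that people with missing later assessments still contribute.

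**The concern.** The completers rule has two parts. The post-measurement part can apply in both arms. The attendance part cannot, because TAU has no training sessions to attend. Read literally, no TAU patient is a completer. Read in the only workable way, TAU+ patients are filtered on attendance and post measurement, and TAU patients on post measurement alone. Attendance arises after randomisation and may be related to prognosis, so the two filtered groups need not be comparable even if the training does nothing.

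The Sample Size section appears to use another notion of completer. It counts 63 in each group and derives them from drop-out, not attendance. The power claimed for the completers analysis therefore does not belong to the set that the Analyses section defines.

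Because the article does not say which analysis decides, a trial with an inconclusive ITT result and a favourable completers result would have no stated rule for its conclusion on suicide ideation.

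**Working it through.** **1. The plan's own figure.** Inputs from Sample Size: "Power calculations are based upon a type I error α = 0.05", "a power of 0.80, and an effect size of 0.5". With SD = 1 and a two-sided test (sidedness is not stated):

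n per group = 2 × (1.960 + 0.842)² / 0.5² = 2 × 7.85 / 0.25 = 62.8, so 63.

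This reproduces "imply a minimum of 63 participants in the groups". A one-sided test would give 50. The power is for a comparison of two equal groups, with no arm-specific selection.

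**2. The rule in each arm.** 80% of 10 sessions is 8.

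| Criterion | TAU+ | TAU |
|---|---|---|
| At least 8 of 10 training sessions | applies | cannot apply |
| Post measurement completed | applies | can apply |

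**3. Size of the bias.** The document gives no attendance rate and no relation between attendance and outcome, so what follows is assumption. Let there be no true effect. Let a share p of TAU+ be non-completers whose outcome is g = 0.5 SD worse than that of completers. The completers' mean is then better than the full arm's mean by p × g. Let a share q of TAU be lost, with gap h.

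Bias in favour of training = p × g − q × h.

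Take p = 0.2, 0.3 and 0.4. The low end and q = 0.2 are borrowed from "a drop out of 20% after randomization". Group sizes are n1 = 75 × (1 − p) and n2 = 75 × 0.8 = 60, and SE = √(1/n1 + 1/n2). With shift s = bias / SE, the two-sided type I error is P(Z > 1.96 − s) + P(Z < −1.96 − s).

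| p | n1 | SE | Bias, h = 0 | Type I | Bias, h = 0.5 | Type I |
|---|---|---|---|---|---|---|
| 0.2 | 60 | 0.183 | 0.10 | 0.085 | 0.00 | 0.050 |
| 0.3 | 52.5 | 0.189 | 0.15 | 0.125 | 0.05 | 0.058 |
| 0.4 | 45 | 0.197 | 0.20 | 0.174 | 0.10 | 0.080 |

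The h = 0 columns treat TAU losses as random. The h = 0.5 columns give them the same gap as TAU+ losses. If non-completers do better instead of worse (g and h negative), the biases change sign and the error rates stay the same.

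**4. Cross-check by another route.** This was a null simulation (20,000 runs) with 75 randomised per arm, all TAU patients kept and only TAU+ attenders kept. Attender share and attendance-outcome correlation are assumed.

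| Attenders | Correlation | Spurious d | Type I |
|---|---|---|---|
| 80% | 0.1 | 0.035 | 0.051 |
| 80% | 0.3 | 0.105 | 0.090 |
| 60% | 0.3 | 0.193 | 0.176 |
| 60% | 0.5 | 0.322 | 0.41 |

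The problem is negligible when attendance hardly relates to outcome and material when it relates moderately. The last row shows that the range in step 3 is an illustration, not a bound.

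**5. Power for ITT alone.** At d = 0.5, a two-means comparison has power 0.865 with 75 per group, 0.801 with 63 and 0.782 with 60.

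**The case against.** **The analyses are not called co-primary.** Reporting ITT beside completers is common, and the ranking may stand in an analysis plan that is not shown. This is right as far as it goes, and a reader who infers that either result alone is meant to establish effectiveness goes beyond the text. But the article itself states both sets, calls both effectiveness analyses and claims power for both. The fault lies in those statements, not in missing detail.

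**TAU is filtered too.** A reader might infer that TAU faces no selection. The post-measurement criterion can apply there, and Sample Size expects completers in both groups. This stands and lowers the figures: with equally selected TAU losses the bias falls to 0.00-0.10 SD and the error to 0.050-0.080. It does not make the two filters alike.

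**Direction and size are unknown.** A reader might infer a spurious benefit of a definite size. Nothing in the document says that poor attenders are the more severe patients. Patients who improve early may also stop attending, which would bias against the training. The planned repeated-measures analysis uses baseline data and would remove part of a stable severity difference, leaving mainly differential change. All of this stands.

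**The ITT wording.** A reader might infer that controls are left out of the ITT set. The Design section describes a two-arm randomised comparison, and the model compares training with treatment as usual. No exclusion of controls is stated. The wording is probably a slip in a sentence about adherence, and needs only an editorial correction.

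**Conclusion.** The point holds in a limited form. As written, one of two unranked effectiveness analyses rests on a set formed after randomisation by a rule that can apply fully only in TAU+. That TAU patients filtered on the post measurement form the comparator is an inference, but the only workable one. Under the stated assumptions the bias runs from about 0 to 0.20 SD, that is, up to 40% of the target d (0.20 / 0.5). Type I error runs from about 0.05 to 0.17. The upper ends require TAU losses to be unselected. The sign depends on whether poor attenders do worse or better. These figures come from a raw comparison of post-treatment scores and will be smaller where baseline data absorb the difference.

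A completers analysis is not an error in itself. The fault is its unranked standing and the power claim attached to it.

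**What to change.** 1. Word the ITT set as all randomised participants in both groups.
2. Name ITT, analysed with the planned repeated-measures mixed model, as the sole basis for the effectiveness conclusion.
3. Label the completers analysis supportive and non-randomised, and state which criterion applies in which arm.
4. Tie the power statement in Sample Size to the ITT analysis only.

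A complier-average causal effect may be added as a sensitivity analysis only. With compliance set at 8 of 10 sessions it assumes that assignment has no effect in patients who attend 1-7. Those patients still receive some training and have the workbook, audio CD and website, so the assumption is doubtful and must be stated.

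The cost is wording, plus one model if the sensitivity analysis is added. The downside is that a favourable completers result could no longer support the effectiveness claim.

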### Experimental Condition

The patients with suicidal ideation who are randomly assigned to the TAU+ condition receive an additional intervention called Future Oriented Group Training. There are 4 to 8 participants in each group, and the sessions are led by one trainer. This intervention consists of three major elements: the training sessions, the workbook with a accompanying audio cd, and a website.

The main goal of this training is to decrease suicidal thinking by stimulating realistic future thinking and reducing hopelessness. The training promotes goal directed and future oriented behavior by combining cognitive therapy, problem solving therapy, and future thinking. This means that participants and trainers almost exclusively address things to come.

The 10 weekly group training sessions last one and a half hours each. They are organized as workshops. Participants listen to the trainer who explains and discusses relevant topics. The trainer asks for personal experiences, but remains on a practical and educational level. The trainer discusses general tendencies, and individual experiences are generalized and reformulated in terms of future oriented cognitions and behavior. How would this kind of thinking, or that way of behaving, influence one's chance of reaching future positive goals? And what can be done about this?

The exercises and texts included in the workbook promote realistic thinking and help participants to create a personal meaningful future, by accomplishing goals that make life worthwhile again. In the workbook notorious cognitive patterns among suicidal patients are challenged, like dichotomous thinking and external locus of control. The participants receive information about suicidal vulnerability and factors influencing this vulnerability, for instance perfectionism, social isolation, and alcohol and drug abuse. The workbook discusses several practical steps, like making a survival plan, and creating a scrapbook with positive elements from their present and their past, in order to find strength when they feel hopeless. The workbook comes with an audio cd, with additional exercises that are in line with the contents of the workbook.

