### Control Condition

Participants in the control condition receive treatment as usual. Our training is additional and does not interfere with the ongoing treatment. In order to be able to compare the TAU and the TAU+ group we gather information on several characteristics of treatment as usual.

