## Discussion

We have developed our Future Oriented Group Training based on the presumption that suicide ideation is characterized by diminished positive future thinking. Our intervention intends to stimulate realistic future perspectives. When suicidal individuals are able to envision a worthwhile future, their hopelessness and suicidal thinking and behavior are expected to decrease.

Extensive research the last twenty years has provided information about the different aspects and dynamics of suicidal thinking and behavior, but only a few interventions for suicidal patients have been evaluated in randomized clinical trials. The ones we know of (for instance Brown et al. [52]) have been developed for patients coming into care after a suicide attempt. Our training aims to help patients early on in the suicidal process, and we include both patients with suicidal ideation and after a suicide attempt in our study.

Future Oriented Group Training combines different elements that have proven to be effective in the treatment of suicidal thinking and behavior, like cognitive therapy and problem solving. Relatively new is the emphasis in the training on future thinking and goal oriented behavior. The intervention is designed to be easy to implement and is suitable for a broad range of comorbid psychiatric disorders.

Treatment programs like our training encompass several potentially effective elements. In the RCT we cannot distinguish which specific factor contributes to what extend to the overall treatment effect. This is also a characteristic of well established treatments, like Dialectical Behavioral Therapy [53]. We obtain an indication of changes in specific areas by gathering data on explanatory factors, like coping, problem solving, and future orientation, but we cannot tell which element of the training is responsible for these changes. Further research might be helpful to discriminate the efficacy of the separate elements.

Stimulating future thinking is a way of helping suicidal individuals to recreate a meaningful life, by working on purposeful goals and overcoming inefficient behavioral and cognitive patterns. The goal of our Future Oriented Group Training is to help our patients to make life livable and maybe even enjoyable again by realistically focusing on what the future might have to offer.

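### Mediating variables are named as candidate covariates for the primary analysis without restriction to pre-randomisation values, so the primary estimate may not be the total effect the trial is sized for

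*Protocol article*

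**What the plan says.** The protocol article, under Analyses, sets the rule for covariates in one sentence, which also covers descriptive variables: "mediating variables will be analyzed in order to reveal variables that need to be taken into account as covariates in the primary analyses". It does not say at which assessment these variables are taken, and that section gives mediators no other role.

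Elsewhere the article describes how the training is meant to work:

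- Experimental Condition: the aim is to "decrease suicidal thinking by stimulating realistic future thinking and reducing hopelessness". The training combines cognitive therapy, problem solving therapy and future thinking.
- Discussion: "When suicidal individuals are able to envision a worthwhile future, their hopelessness and suicidal thinking and behavior are expected to decrease".
- Discussion, on the process measures: "We obtain an indication of changes in specific areas by gathering data on explanatory factors, like coping, problem solving, and future orientation".

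The process measures under Explanatory variables are the CISS, the adapted FTT, the ZTPI with its transcendental scale (TFTPI), and the SPSI-R. Hopelessness (BHS) is listed under Secondary Outcomes. The Design section sets assessments at entry, three months and one year.

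The quantity of interest under Analyses is Cohen's d on suicide ideation, with an intention-to-treat analysis. Sample Size plans for d = 0.5, alpha 0.05 and power 0.80, giving at least 63 per group.

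**The concern.** A mediator is a variable that treatment changes and that in turn changes the outcome. If its post-randomisation value enters the model for the treatment effect, the treatment coefficient no longer measures the whole difference between TAU+ and TAU. It measures only the part that does not pass through the mediator. Randomisation no longer protects even that part, because anything that affects both the mediator and suicide ideation now confounds it.

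This conflicts with the article's own aims. It wants the overall effect on suicide ideation by intention to treat, and it sizes the trial for that effect. Under the covariate rule as worded, the better the training works by its intended route, the smaller the adjusted effect could be. A training that works could be reported as having little or no effect.

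A second, lesser matter is that the covariates are to be found by analysing trial data, and there are many candidates: five process instruments, several with subscales, plus the descriptive variables. To the extent that outcome data guide the choice, the primary estimate comes from a model picked after the fact.

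**Working it through.** **1. The plan's own figure.** Inputs from Sample Size: d = 0.5, alpha = 0.05 (taken as two-sided), power 0.80. By the normal approximation,

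n per group = 2 × (1.960 + 0.842)² / 0.5² = 62.8, rounded up to 63.

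This reproduces the stated 63. The t-test version gives 63.8, so 64. A one-sided test would need 50, so the stated figure is two-sided. Power at 63 per group is 0.80. The trial is therefore sized for a total effect of 0.5 SD.

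**2. Which variables are on the path.** The passages, set side by side:

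| Place in the article | Role given to the variables |
|---|---|
| Experimental Condition | future thinking and hopelessness are what the training acts on to lower suicidal thinking |
| Discussion | envisioning a worthwhile future comes first; lower hopelessness and suicidal thinking follow |
| Discussion | changes in coping, problem solving and future orientation are to be observed |
| Analyses | mediating variables are candidates for covariates in the primary analyses |

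The first three describe variables that the training may change. The fourth admits mediating variables to the primary model with no limit on timing.

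**3. Size if post-randomisation values are selected.** The article gives no mediated share, so a range is assumed. Let a be the shift in the mediator due to training, b the mediator-outcome slope, and m the mediated share, all in SD units. Then

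total effect = direct effect + a × b, with m = a × b / 0.5.

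Assume a = 0.5, so that b = m. Assume also a within-arm outcome SD of 1 and no mediator-outcome confounding. Then:

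- direct effect = 0.5 × (1 − m)
- residual SD after adjustment = √(1 − b²)
- variance inflation, because the mediator is correlated with arm = 1 + a²/4 = 1.0625
- standard error = √(1 − b²) × √(2/63) × √1.0625

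For m = 0.50, the standard error is 0.866 × 0.178 × 1.031 = 0.159. The ratio is 0.25 / 0.159 = 1.57, and power is Φ(1.57 − 1.96) = 0.35. A simulation of the same model (63 per arm, 4,000 replicates, t-tests) gave:

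| Mediated share (assumed) | Estimate, no mediator in model | Power | Estimate, mediator in model | Power |
|---|---|---|---|---|
| 25% | 0.50 | 0.80 | 0.38 | 0.56 |
| 50% | 0.50 | 0.79 | 0.25 | 0.34 |
| 75% | 0.50 | 0.79 | 0.12 | 0.17 |

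Shrinking d while leaving the SD at 1 gives power of 0.56, 0.29 and 0.10. The simulated figures are higher at the larger shares because adjustment also reduces residual variance. That gain does not make up for the lost effect.

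**4. After correction.** With no post-randomisation mediator in the model, the target stays at d = 0.5, power at 63 per group stays at 0.80, and the planned number is unchanged.

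**The case against.** The strongest reply is that the article does not commit to the harmful model. Variables are to be analysed to see which ones matter, so entry depends on that screening. No mediator is named as a covariate and no time point is given. Baseline values of the CISS, FTT, ZTPI or SPSI-R would remove none of the treatment effect. The word *mediating* appears only once and may be loose usage for prognostic variables. The Discussion treats the process measures as results to report, and the BHS is listed as a secondary outcome.

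Part of this stands. A reader might infer that mediators are certain to be entered; the text supports only that they are candidates. But a baseline value does not mediate anything, so the literal wording points to post-randomisation values. If baseline values were meant, the sentence still needs correcting. An analysis plan that followed the sentence would carry the fault forward, so this is not merely detail left to a fuller document.

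Two other stronger readings are not supported:

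- *That treatment-as-usual characteristics will also be adjusted for.* Control Condition says "we gather information on several characteristics of treatment as usual" so that the two groups can be compared. It does not make those characteristics covariates.
- *That the primary p-value is invalid.* This depends on whether screening uses outcome data and how. The article does not say, and selection rules are commonly left to the full protocol or analysis plan.

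**Conclusion.** The concern holds in a limited form. The covariate sentence under Analyses is wrong as written: it makes mediating variables eligible for the primary treatment-effect model without confining them to pre-randomisation values, while the article's theory places such variables between the training and suicide ideation. If post-randomisation values are selected, the estimate becomes a direct effect open to confounding, not the total effect of 0.5 SD for which the trial is sized.

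The size is conditional. With assumed mediated shares of 25% to 75%, a mediator shift of 0.5 SD and no mediator-outcome confounding, d falls to about 0.38 to 0.12 and power at 63 per group from 0.80 to roughly 0.56 to 0.17. These figures illustrate the risk and do not predict this trial's loss. Real confounding between mediator and outcome could move the estimate further in either direction. Post hoc selection of covariates is a secondary weakness, to the extent that outcome data guide it.

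Because the fault bears on the primary estimate and is easily removed, it should be corrected before analysis.

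**What to change.** Rewrite the covariate sentence under Analyses so that:

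- *mediating* is deleted from the covariate step;
- covariates in the primary model are a short list of pre-randomisation variables, fixed in advance and not searched for in the trial data;
- the list includes baseline SSI and, for example, hospital or in-patient/outpatient setting if these are recorded (Participants describes them, but Sample characteristics does not list them among the data gathered);
- post-baseline CISS, FTT, ZTPI/TFTPI, SPSI-R and BHS values are kept out of the primary model, and where they are used to explain the effect, this is done only in a separate mediation analysis labelled exploratory.

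The BHS remains a secondary outcome as planned. If the authors meant baseline values of the process measures, the sentence should say so and name them.

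The cost is a sentence or two of text. The core change needs no new data, and the sample size is unaffected.

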## Background

Suicide has a low prevalence in the general population, but suicide ideation is remarkably common [1]. In The Netherlands about 10% of the general public reported that they ever had suicidal thoughts [2], and Casey et al. [3] found no differences amongst several European countries. When these patients enter treatment, they are confronted with a commonly held misconception amongst health care workers that suicidal thinking and behavior will vanish when underlying psychiatric problems are treated. We have very good reasons to believe this is not the case. Suicidal thinking fluctuates over time [4,5], and reoccurs in the majority of depressed individuals in a consecutive episode [6]. In a study amongst formerly suicidal patients, Williams et al. [7] showed that problem-solving abilities and autobiographical memory specificity, commonly associated with suicidal thinking and behavior, deteriorate when the patient's mood lowers again. Suicidality appears to become a syndrome irrespective of underlying psychiatric morbidity [8]. This is a reason for Oquendo et al. [9] to plea for a separate diagnostic category in the forthcoming DSM classification manual. A distinct psychiatric problem, which needs a specific intervention.

Clinicians in psychiatry are increasingly aware of the need for systematically assessing suicidal risk, but they lack the tools for addressing suicidal thinking as a specific goal in treatment. There is a shortage of well described, evidence based treatment methods for suicidal behavior and suicide ideation. A few randomized clinical trials focussing on self harm and suicidal behaviour have been published, like MACT [10] (Manual Assisted Cognitive- Behavior Therapy) and the study on cognitive therapy for suicide attempters by Brown et al. [11]. There are studies on suicidality as a component of treatment programs for borderline patients, like Dialectical Behavioral Therapy [12,13], Schema Focussed Therapy [14], and Mentalization Based Treatment [15]. Most of these interventions have been applied in the Netherlands, but they all are developed for specialized settings and specific patient groups. A reason for us to develop an intervention for a broad group of patients with suicidal thoughts. This new intervention should be easy to implement as an add on intervention. Therefore, it should not require highly specialized therapists.

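### The Analyses section does not secure adjustment for baseline SSI; if the test is an unadjusted change contrast, power can fall below the planned 0.80

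*Protocol article*

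**What the plan says.** All references are to the protocol article.

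- **Design:** SSI, the primary outcome, is measured at entry, at three months and at one year.
- **Analyses:** the arms are to be compared as follows: "we will perform analyses of repeated measures". The model is multilevel with participant-level random effects, which "permits estimation of changes in repeated measures" when some later assessments are missing. Covariates for the primary analysis are to be identified by first analysing background characteristics and mediators. Baseline SSI is not mentioned in that step. The text does not say whether baseline SSI is a response with its own mean in each arm, a response with one shared mean, or a covariate.
- **Sample Size:** at the 5% level and 80% power, the stated result is "an effect size of 0.5, imply a minimum of 63 participants in the groups". No correlation between visits enters.
- **Background:** "Suicidal thinking fluctuates over time". No over-time correlation for the SSI is given anywhere. The SSI coefficients under Primary Outcome are internal consistency and interrater agreement, which say nothing about stability over months.

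**The concern.** A repeated-measures model that describes change over three visits, with baseline as one of the responses, is often fitted as a group-by-time interaction with a free baseline mean in each arm. That contrast is the difference in change from baseline. It carries the noise of the baseline measurement in full and is more precise than a plain follow-up comparison only when baseline and follow-up are strongly enough correlated. The sample size rests on the plain comparison and leaves no margin. For an outcome that the article itself calls fluctuating, followed for a year, a low correlation cannot be ruled out.

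At stake is precision, and with it power. Both contrasts are unbiased under randomisation. Adjustment for baseline SSI uses data already collected and also deals with chance imbalance at entry. Under the wording in Analyses, whether it happens depends on how the model is parameterised and on what the covariate search turns up.

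**Working it through.** **Inputs from the article (Sample Size):** α = 0.05, power 0.80, d = 0.5, 63 per group, 1:1 allocation. The number of sides is not stated.

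**Assumptions:** two-sided test; d = 0.5 on the raw SSI SD; equal SDs at each visit; r is the baseline-to-follow-up correlation, not in the article, shown for 0.2 to 0.7.

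**1. The plan's own figure.** n = 2(1.96 + 0.8416)²/0.5² = 62.8, so 63 per group. This matches; a one-sided test would give 50. Power at 63 is Φ(0.5/√(2/63) − 1.96) = Φ(2.806 − 1.96) = 0.801. The formula is a two-group comparison of one measurement, with no baseline term.

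**2. Variance factors relative to that comparison (single visit).**
- Follow-up only: 1
- Change from baseline: 2(1 − r)
- Baseline-adjusted: 1 − r²

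The ratio of change to adjusted is 2(1 − r)/(1 − r²) = 2/(1 + r). A generalised least squares check of a random-intercept model, with two and with three visits, gave the same powers as these formulas: free arm baselines reproduce the change score, and a common baseline mean reproduces the adjusted analysis.

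**3. Power at 63 per group**, Φ(2.806/√factor − 1.96), and n per group for 0.80:

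| r | Change: power (n) | Adjusted: power (n) | Variance ratio |
|---|---|---|---|
| 0.2 | 0.602 (101) | 0.817 (61) | 1.67 |
| 0.3 | 0.660 (88) | 0.837 (58) | 1.54 |
| 0.4 | 0.726 (76) | 0.865 (53) | 1.43 |
| 0.5 | 0.801 (63) | 0.900 (48) | 1.33 |
| 0.6 | 0.881 (51) | 0.939 (41) | 1.25 |
| 0.7 | 0.952 (38) | 0.976 (33) | 1.18 |

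The change contrast matches the planned power when 2(1 − r) = 1, that is at r = 0.5.

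**4. Both follow-up visits averaged (equal correlations).** The change factor is (1 + r)/2 + 1 − 2r = 1.5(1 − r), which equals 1 at r = 1/3. Change power is 0.726, 0.782, 0.841 and 0.900 at r = 0.2, 0.3, 0.4 and 0.5. Adjusted power is at least 0.96 throughout.

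**5. Unequal SDs.** If the baseline SD is s times the follow-up SD, the change factor is 1 + s² − 2rs and its break-even is r = s/2. Its excess over the adjusted factor is 1 + s² − 2rs − (1 − r²) = (s − r)², never negative. So the size of the loss depends on s, but the ordering does not.

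**The case against.** The strongest reply is that the article does not say baseline is left unadjusted. A mixed model with a common baseline mean is also a multilevel repeated-measures analysis of change, and baseline SSI could enter through the covariate step. The sentence containing "permits estimation of changes in repeated measures" mainly explains how missing assessments are handled; it does not define the primary contrast. A full protocol or analysis plan may fix the parameterisation. This stands. A reader might infer that the plan definitely omits baseline SSI, and the text does not support that. What remains is narrower: the article does set a route to primary-analysis covariates, and that route does not guarantee the one covariate most likely to matter.

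The size of the loss is also open to challenge. The article does not give r, and fluctuation suggests a low value without establishing one. Entry on suicidal ideation could lower r but could also shrink the baseline SD. With s = 0.7 (assumed) and r = 0.3 the change factor is 1 + 0.49 − 0.42 = 1.07, not 1.4, and power at 63 per group is Φ(2.806/√1.07 − 1.96) ≈ 0.77, not 0.66. The article names neither the SD behind d nor a single-visit contrast. These points stand as limits on the figures.

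A reader might also infer that adjustment always makes good the separate dropout shortfall in Sample Size, where 75 × 0.8 = 60 per group remain, not 63. It does so only if 1 − r² < 60/63, that is r above about 0.22; at r = 0.2 and 60 per group adjusted power is 0.798. That shortfall is a different matter and is kept out of the table.

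**Conclusion.** The concern holds in conditional form. The Analyses section leaves adjustment for baseline SSI unsecured but does not exclude it. If the test turns out to be a group-by-time contrast with free arm baselines, it is less precise than the adjusted contrast: by a variance ratio of 1.54 at r = 0.3 and 1.25 at r = 0.6. Whether it also misses the planned 0.80 depends on r: below 0.5 for a single visit, below about 0.33 for the two-visit average, and not otherwise. These thresholds rest on 63 per group, equal SDs and d on the raw SD. That the adjusted contrast is at least as precise needs none of these; it is a large-sample result, and estimating one regression slope costs a negligible amount. This is a point about efficiency and prespecification, not about bias.

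**What to change.** State the primary model in one of two equivalent ways:

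- a mixed model of SSI at 3 and 12 months with baseline SSI and its interaction with time as covariates; or
- a constrained longitudinal model in which all three visits are responses and the baseline mean is common to both arms.

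In either case, say that baseline SSI is in the model regardless of the covariate search. The treatment effect is then the adjusted difference between arms at the named time point.

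The cost is one sentence of analysis wording. No new data are needed, and the sample size does not have to change on this account. If a fuller protocol or analysis plan already contains this, it is enough to make the article's wording consistent with it.
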